Recent surveys in the United States and Europe demonstrated that although the use of remote monitoring is growing, overall adaptation remains low and varies considerably between hospitals [8, 9]. Impediments to implementation include the absence of national guidelines and reimbursement models for remote monitoring in clinical practice [4, 6, 9–11]. Also, remote monitoring is unlikely to become the standard of care until it is conclusively demonstrated that patient outcome is favourably affected [12, 13]. Whether clinical effects of remote monitoring translate into improved patient-reported outcomes such as symptoms, quality of life and satisfaction with care, and whether patients are more satisfied with remote monitoring than in-clinic follow-up has received little attention.

To date, the few randomised controlled trials on remote monitoring in ICD patients that included patient-reported outcomes have yielded inconsistent results [14–16]. Prospective cohort studies using short ad hoc questionnaires have reported that 60–95 % of ICD patients are highly satisfied with remote monitoring and that it makes them feel safe [17–22]. However, these studies provided no information on how many patients refused to use a remote monitoring system and preferred to be checked at the outpatient clinic. This is essential, as a recent registry study from the United States showed that 24 % of the patients who received a remote monitoring system did not activate it [8].

No prospective randomised study has examined whether there is a subset of patients who might not benefit from remote monitoring in terms of patient-reported outcomes and might be more satisfied with standard clinical follow-up visits. For example, a substantial number of ICD patients report increased emotional distress, such as anxiety and depression [23]. The remote monitoring system might provide these patients with a sense of security, but on the other hand the system may act as a constant reminder of their device and underlying disease. Also, patients might miss the personal attention and reassurance from their treating physician and heart failure team [24]. A qualitative study on ICD patients who received a remote monitoring system showed that nonusers believed that in-clinic visits are psychologically advantageous and trusted the healthcare professionals over technology when it came to managing their health [25].

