The international REMOTE-CIED study is the first prospective, randomised controlled study primarily designed to examine the patient perspective on remote monitoring in ICD patients, in order to enhance the patient-centredness of care in this patient group. The primary study objective is to evaluate the influence of remote patient monitoring versus conventional in-clinic follow-up on patient-reported outcomes, by means of standardised and validated questionnaires. Secondary objectives are to (1) identify subgroups of patients who might not be satisfied with remote monitoring and examine if they are distinguishable based on their demographic, clinical, or psychological profile; and (2) investigate the cost-effectiveness of remote monitoring + in-clinic follow-up as compared with in-clinic follow-up only.

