### Study procedure, randomisation and follow-up

When scheduled for device implantation, eligible patients receive a letter describing the purpose, design and possible benefits/risks of the study. Patients willing to participate are asked to sign an informed consent form. Of note, study refusal or withdrawal due to the patient having a strong preference for remote monitoring or in-clinic follow-up will be registered.

At discharge from hospital after implantation, included patients receive the baseline questionnaire and are asked to complete this 1 to 2 weeks after implantation (T_0_) to avoid measuring preoperative distress. When the completed T_0_ questionnaire is received at Tilburg University–which serves as core lab for the patient-reported outcomes–patients are randomised in a 1:1 fashion to either remote patient monitoring + in-clinic follow-up (RPM group) or in-clinic follow-up only (In-Clinic group) with the use of a blocked randomisation procedure. To ensure that the relative percentage of ICD and CRT-D patients is equal in both groups, we use separate randomisation procedures within these two subsets of patients.

Four to 8 weeks after implantation (preferably during the first in-clinic visit for assessment of wound healing etc.), patients in the RPM group will receive the remote monitoring system and be instructed how to install and use it. In accordance with the ACC/AHA/HRS guidelines, patients randomised to this group will visit the outpatient clinic again at 12 and 24 months after implantation [2]. The intermediate check-ups will be performed remotely. Patients randomised to the In-Clinic group will be followed up according to standard practice at the participating centres and visit the outpatient clinic (at least) every 3–6 months during the study. For patients in both groups, the follow-up assessments will take place at 3 (T_1_), 6 (T_2_), 12 (T_3_), and 24 (T_4_) months post-implantation. A schematic representation of the study design is shown in Fig. 1.

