### Measures

Primary endpoints are patient-reported heart failure-specific health status (i.e., symptoms, functioning and quality of life), ICD acceptance and satisfaction with care. To assess these patient-reported outcomes and potentially associated psychological factors (i.e., Type D personality, psychological distress), patients in both groups will complete a number of questionnaires at the five assessment times (Table 1). All questionnaires are standardised and validated, except for the questionnaires used to assess patient satisfaction with remote monitoring, and their productivity and healthcare utilisation for cost-effectiveness. For these purposes, new questionnaires were developed.

**Table 1 Tab1:** Patient-reported outcomes and psychological factors assessed in the study

Construct	Questionnaire	T_0_	T_1_	T_2_	T_3_	T_4_
Outcome measures						
Health status	Kansas City Cardiomyopathy Questionnaire (KCCQ)	x	x	x	x	x
Device acceptance	Florida Patient Acceptance Survey (FPAS)	x	x	x	x	x
Satisfaction with care	Visual analogue scale (0–100)	x	x	x	x	x
Satisfaction with remote monitoring^a^	Purpose-designed questionnaire		x	x	x	x
Cost-effectiveness: QALY	Euroqol 5D (EQ-5D) + VAS scale	x	x	x	x	x
Cost-effectiveness: productivity and health care utilisation	Purpose-designed questionnaire		x	x	x	x
Psychological variables						
ICD concerns	ICD Patient Concerns Questionnaire (ICDC)	x		x	x	x
ICD expectations^b^	Expectations regarding ICD	x				
Illness perception	Illness Perceptions Questionnaire (IPQ)	x			x	
Anxiety symptoms	Generalised Anxiety Disorder (GAD-7)	x			x	x
Depressive symptoms	Patient Health Questionnaire (PHQ-9)	x			x	x
Type D personality	Type D Scale (DS14)	x				
Self-care behaviour	European Heart Failure Self Care Behaviour Scale (EHFScBS)	x			x	x

T_0_ = Baseline; T_1_ = 3 months; T_2_ = 6 months; T_3_ = 12 months; T_4_ = 24 months

*ICD* implantable cardioverter defibrillator; *QALY* quality-adjusted life year; *VAS* visual analogue scale

^a^Patients in RPM group only

^b^Dutch patients only

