### Sample size calculation and statistical analyses

The number of patients required to provide sufficient power to test the first objective of the proposed study was derived from a power analysis based on a small expected between-group effect size of .20, as measured with Cohen’s *d*. With alpha = 0.05 and power = 0.85 (two-sided test), 900 patients are needed (i.e., 450 in each group). The data will be analysed according to the intention-to-treat principle, with the inclusion of all randomised patients in the statistical analysis regardless of whether they completed the study.

Univariable and multivariable linear and logistic regression analyses will be performed to examine the group effects on health status, device acceptance and satisfaction with care at several points in time. Analysis of (co)variance with repeated measures will be performed to assess between-group differences in changes in these patient-reported outcomes over 2 years.

Patients’ answers on the ‘Satisfaction with remote monitoring’ questionnaire will be used to classify them into subgroups of patients that are/are not satisfied with remote monitoring. Chi-square tests and Student’s t-tests (or a non-parametric equivalent if necessary) will be performed to explore the demographic, clinical, and psychological characteristics of the patients in these subgroups. Also, multivariable logistic and linear regression analyses will be performed to examine which factors are independently associated with satisfaction with remote monitoring as a dichotomous outcome (satisfied: yes/no) and as a continuous outcome (satisfaction visual analogue scale 0–10), respectively.

To determine the cost-effectiveness, both short-term and long-term country-specific cost-effectiveness analyses will be performed. The short-term analysis has a 2-year time horizon, while the long-term analysis will have a lifetime horizon. Data used for the short-term analysis will be based on the data captured during the trial, while data used for the long-term analysis will consist of a combination of trial data and data from other sources. These data will be combined using a disease progression and treatment model and will be analysed using probabilistic analyses, sensitivity analyses, and scenario analyses. The primary cost-effectiveness outcome will be the incremental cost per quality-adjusted life year (QALY) gained.

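### Satisfaction with remote monitoring is classified from questionnaire answers alone, so patients in the remote arm who withdraw for preference and never answer are left out of the search for dissatisfied patients

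*Protocol article*

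**What the plan says.** The first secondary objective is to "identify subgroups of patients who might not be satisfied with remote monitoring and examine if they are distinguishable" by demographic, clinical or psychological profile. For this, the section on sample size and statistical analyses says that answers on the satisfaction questionnaire "will be used to classify them into subgroups of patients that are/are not satisfied with remote monitoring". The two groups are then compared. Logistic regression is planned for the yes/no outcome and linear regression for a 0–10 visual analogue scale, which is also self-reported.

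Table 1 (Measures) schedules the questionnaire at 3, 6, 12 and 24 months, with the footnote "Patients in RPM group only".

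The Introduction says of earlier cohorts that "these studies provided no information on how many patients refused to use a remote monitoring system and preferred to be checked at the outpatient clinic". It calls this information essential, citing a US registry in which "24 % of the patients who received a remote monitoring system did not activate it".

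The section on study procedure and randomisation states that "study refusal or withdrawal due to the patient having a strong preference for remote monitoring or in-clinic follow-up will be registered". The statistical section does not mention this record. It does state an intention-to-treat principle covering all randomised patients, but does not say how that applies to an analysis within one arm.

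**The concern.** The analysis is meant to find the patients whom remote monitoring does not suit. A patient who leaves the study after allocation to remote monitoring because of a preference for clinic visits is among the clearest such cases. If satisfaction status can come only from a questionnaire, and that patient never returns one, the patient is in neither group and in neither regression.

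This loss would be selective. It would remove patients from the not-satisfied side, make the satisfied share look higher, and leave the predictor analysis to be fitted on those who accepted the system well enough to keep responding. Characteristics that go with early rejection of remote monitoring could then be missed. The Introduction names this kind of gap as the weakness of earlier work.

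**Working it through.** **The plan's own figure.** The article gives 900 patients, 450 per group, for d = 0.20, two-sided alpha 0.05 and power 0.85. The normal approximation is n per group = 2(z₀.₉₇₅ + z₀.₈₅)²/d² = 2(1.960 + 1.036)²/0.04 ≈ 449, or 898 in total. The t-test version gives 449.9, so 450 per group and 900 in total. The figure reproduces. It is sized for the first objective and this point does not affect it. It only supplies the 450 used below.

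**Timeline.**
- Baseline questionnaire (T0): 1–2 weeks after implantation.
- Randomisation: when the completed T0 questionnaire is received.
- Remote monitoring system handed over: 4–8 weeks after implantation.
- First satisfaction questionnaire (T1): 3 months.

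A patient can therefore learn the allocation, or receive the system, and withdraw before any satisfaction answer is due. That patient has T0 data and may have a registered reason for withdrawal, but cannot be classified under the stated rule.

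**Illustration of size.** The documents give no rate of preference withdrawal, so the rates here are assumptions. Let N = 450, f = the share who leave or do not use the system and give no answers, and d = the share not satisfied among the rest.
- Share seen by the questionnaire rule: d.
- Share of the arm if the silent patients count as not satisfied: [d(1 − f)N + fN]/N.

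Case 1, f = 5% and d = 10% (both assumed):
- Silent patients: 0.05 × 450 = 22.5. The rest: 427.5.
- Not satisfied among the rest: 0.10 × 427.5 = 42.75.
- Share of the arm: (42.75 + 22.5)/450 = 65.25/450 = 14.5%, against 10%.
- Share of not-satisfied patients missed: 22.5/65.25 = 34%.

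Case 2, upper bound, f = 24% (the registry figure in the Introduction) and d = 5% to 40% (the complement of the 60–95% highly satisfied in earlier cohorts):
- Silent patients: 0.24 × 450 = 108. The rest: 342.
- d = 5%: (17.1 + 108)/450 = 27.8%.
- d = 40%: (136.8 + 108)/450 = 54.4%.

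Case 2 is a ceiling for three reasons. It assumes that no non-user answers and that every non-user is dissatisfied, and it treats anyone short of highly satisfied as not satisfied.

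**The case against.** A reader might infer that everyone in the remote arm who declines, never activates or hands back the system drops out of this analysis. The article does not say so. Table 1 assigns the questionnaire to the arm as randomised, not to active users. A non-user who stays in the study is due four questionnaires and can be classified as not satisfied. Someone who returns the system after 3 months may already have answered. This part of the objection stands, and it limits the point to patients who stop responding.

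A reader might also infer that the trial simply repeats the flaw it criticises. That goes too far. Earlier studies had no count of refusers, whereas this trial registers preference-driven refusal and withdrawal. What is missing is the link from that record to the satisfaction analysis.

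Nor should 24% be read as the expected loss. It comes from an outside registry and is not a planning assumption. Patients here consented to randomisation, and those with strong preferences could refuse beforehand. The documents also state no satisfaction rate as an endpoint, so the effect on which patients are characterised matters more than the shift in a percentage.

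Finally, the article is condensed. Scoring, cut-off and handling of missing answers are commonly left to a full protocol or analysis plan, which are not shown and may deal with this. That is fair for those details. But the article does fix the source of the classification, and followed as written that source cannot classify a patient who gives no answers. The intention-to-treat sentence does not solve this, because including a patient does not assign that patient a satisfaction status.

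**Conclusion.** The point holds in a limited form. Classification from questionnaire answers alone leaves out patients randomised to remote monitoring who withdraw because they prefer clinic follow-up and return no satisfaction questionnaire. This bears on the first secondary objective. The between-group comparisons and the sample size are unaffected.

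The size cannot be determined from the documents. The move from 10% to about 15% rests on an assumed 5% silent preference withdrawal and an assumed 10% not satisfied among the rest. The range of 28% to 54% is an upper bound and should not be quoted as an estimate. If few patients withdraw in this way, the effect will be small, and the added analysis will show that.

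**What to change.** Keep the questionnaire-based classification as planned. Add an analysis over all patients randomised to remote monitoring in which registered preference-driven withdrawals against remote monitoring count as not satisfied, or form a category of their own. Use T0 characteristics as predictors. They exist for every randomised patient, because randomisation waits for the completed T0 questionnaire. Report refusals before randomisation separately, since those patients belong to neither arm.

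The cost is some wording in the analysis plan and one further analysis, with no new visits or questionnaires. The withdrawal reason is already to be registered. Activation and return of the system are not among the clinical data listed in the Measures section, so the added analysis should not depend on them unless they are shown to be collected.

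The drawbacks are a lower satisfied share and a mixed construct: leaving for preference is not the same as rating a system one has used as unsatisfactory. For that reason both results should be shown side by side.

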## Discussion

Large-scale trials have shown that remote patient monitoring is a safe, effective and timely alternative for conventional in-clinic follow-up of ICD/CRT-D patients [6]. However, these trials have fallen short in their patient-centredness and have left an important question unanswered: namely, what do patients think about remote monitoring [12]? To date, evidence on the patient perspective on remote monitoring is scarce and inconsistent. As emphasised in a recent scientific statement from the American Heart Association, the assessment of patient-reported outcomes such as patient-reported health status is essential to enhance the patient-centredness of care and better characterise the impact of healthcare delivery on patient health [26]. No study has examined whether there is a subset of patients who might not benefit from remote monitoring in terms of patient-reported outcomes and would be more satisfied with standard clinical follow-up visits, and whether they are distinguishable based on their demographic, clinical, or psychological profile. The REMOTE-CIED study is an international, prospective randomised controlled study specifically designed to provide more insight into the patient perspective on and cost-effectiveness of remote monitoring compared with in-clinic follow-up in ICD/CRT-D patients. This study will be able to show how patients feel about remote monitoring and determine whether there are subgroups of patients that might be better served by receiving in-clinic follow-up visits. The study aims to include 900 consecutive patients from five European countries, who will be followed-up for 2 years post-implantation.

## Conclusion

The international REMOTE-CIED study is the first prospective randomised controlled study that primarily aims to assess the effect of remote patient monitoring on patient-reported outcomes in ICD patients, which could help to support patient-centred care in the future. The study is currently recruiting patients and results are expected in 2017.
